**Methods:**

The study is a pragmatic, randomised, controlled trial in outpatients with epilepsy. Participants are randomly assigned to one of two follow-up activities: a) standard telePRO or b) open access telePRO. Inclusion criteria are age ≥ 15 years and previous referral to standard telePRO follow-up at Aarhus University Hospital, Denmark. Furthermore, patients must have answered the last questionnaire via the Internet. The number of contacts will be used as the primary outcome measure. Secondary outcome measures include well-being (WHO-5 Well-Being Index), general health, number of seizures, treatment side effects, mortality, health literacy (Health Literacy Questionnaire), self-efficacy (General Self-Efficacy scale), patient activation, confidence, safety, and satisfaction. In addition, the patient perspective will be explored by qualitative methods. Data will be collected at baseline and 18 month after randomisation. Inclusion of patients in the study started in January 2016. Statistical analysis will be performed on an intention-to-treat and per-protocol basis. For qualitative data, the interpretive description strategy will be used.

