### Study timeline

Inclusion and randomisation with baseline assessments will take place from January 2016. Follow-up assessment will take place 18 months after randomisation. Baseline and follow-up assessments are shown in Table 1. Figure 4 presents the inclusion of patients and the stages in the study.

**Table 1 Tab1:** Primary and secondary outcomes, data sources, and timeline for measurements

Outcomes	Data sources	Measurement/month
Resource utilisation		
1. Number of contacts	The Hospital Business Intelligence Register, Central Denmark Region	0–18
Quality of care		
2. Well-being	WHO-Five Well-being Index (WHO-5)	0, 18
3. General health	Item from The Short Form Health Survey (SF-36)	0, 18
4. Mortality	The Hospital Business Intelligence Register, Central Denmark Region	0–18
5. Number of seizures	Item from the epilepsy questionnaire, Central Denmark Region	0, 18
6. Treatment side effects	Item from the epilepsy questionnaire, Central Denmark Region	0, 18
Patient perspective ^a^		
7. Health literacy	The Health Literacy Questionnaire (HLQ) sub scale 4, 6 and 9	0, 18
8. Self-efficacy	General Self-Efficacy scale (GSE)	0, 18
9. Patient activation	Items from Patient Activation Measure (PAM)	0, 18
10. Confidence, safety, and satisfaction	Items from a PREM questionnaire, Danish Cancer Society	0, 18

^a^ The patient perspective is primarily explored by qualitative methods in a complementary PhD study

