### Sample size

Statistical power was estimated for the primary outcome number of contacts. Based on literature review [32] the number of consultations (n) and standard deviation (SD) was; *n* = 4.64, (SD = 2.38) in conventional follow-up and *n* = 4.12, (SD = 3.41) in open access follow-up. We expect at least a difference of one contact between the groups. Given a statistical power of 90%, *p*-value 0.05, and allocation ratio 0.8, we will need a sample size of 172 patients in the standard telePRO group and 214 patients in the open access telePRO group. To account for attrition and loss to follow-up, we will recruit a total of approximately 500 participants. For qualitative data, a purposeful sample of at least five participants from each group will be interviewed.

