### Analyses

Descriptive statistics will be used to describe differences in the baseline characteristics of participating patients in the two arms of the trial. Statistical analysis will be intention to treat, whereby all randomised participants will be included in the analysis according to their randomised allocation. The primary outcome, total *number of contacts* in the two arms*,* will be analysed using a sample t-test. If the distribution of data is skewed, we will use medians and nonparametric tests. For secondary outcomes, a chi-square test or logistic regression will be used for dichotomous outcome data and sample *t*-test or multiple linear regression analysis will be used for continuous outcome data. Non-parametric tests will be used if continuous data are not normally distributed. Demographics covariates (sex, age, education, marital status, and epilepsy diagnosis duration) will be included in the per- protocol analysis.

For qualitative data, ID will be employed as the overriding research approach. ID is an inductive research strategy in which constant comparative method with concurrent data collection and analysis is utilised to gain a deeper insight and understanding of human experiences within their natural context. The result is a comprehensive interpretation, potentially a *model of explanation* of the phenomenon under study, which can provide clinical practice with a research-based choice of action [31]. ID is considered appropriate in the present study because the approach is suited for exploration of specific clinical issues, in this case how patients with epilepsy experience standard and open access telePRO follow-up.

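### Baseline scores are collected for every questionnaire outcome, but no analysis is stated to use them: the continuous secondary outcomes are left to a t-test, an unspecified regression or a rank test

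*Protocol article*

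**What the plan says.** The Abstract gives the schedule: "Data will be collected at baseline and 18 month after randomisation". Table 1 under Study timeline repeats it outcome by outcome, for example "WHO-Five Well-being Index (WHO-5) 0, 18". The same two time points stand against general health, seizures, side effects, the three HLQ subscales, GSE, the patient activation items and the confidence, safety and satisfaction items.

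Under Analyses, continuous secondary outcomes get a t-test "or multiple linear regression analysis will be used for continuous outcome data". Dichotomous ones get a chi-square test or logistic regression. A further rule follows: "Non-parametric tests will be used if continuous data are not normally distributed". The section does not say when regression replaces the t-test, what the regression contains, or whether the 18-month value or the change from baseline is compared.

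Covariates are named once: "Demographics covariates (sex, age, education, marital status, and epilepsy diagnosis duration) will be included in the per- protocol analysis". The one use stated for baseline data is descriptive: "Descriptive statistics will be used to describe differences in the baseline characteristics of participating patients".

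**The concern.** When a score is measured before and after, its own baseline value is usually the strongest available predictor of the later value. Here it is on hand for all the questionnaire outcomes. It is also a sound covariate. Under Randomisation, both arms receive the baseline questionnaire with the routine one, and intervention patients are told about open access only two weeks after the clinician has responded. The score therefore precedes the intervention.

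Precision matters on these outcomes for three reasons:
- The sample size was set for number of contacts alone.
- The Discussion expects small differences between two similar forms of follow-up.
- Hypothesis 2, that quality of care is no worse under open access, can be supported only by a reasonably narrow interval.

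A t-test on the 18-month scores, or a rank test, would leave the baseline information unused. The only adjustment that is spelled out belongs to the per-protocol analysis and omits the baseline score.

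**Working it through.** **1. Numbers analysed.** The article gives no precision or power for the secondary outcomes, so its sample size for contacts, 172 + 214 = 386, serves as the basis. The inputs (Sample size section) are a difference of 1 contact, 90% power, significance level 0.05 (taken as two-sided), ratio 0.8, "SD = 2.38) in conventional follow-up" and "SD = 3.41) in open access follow-up".

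With n₁ = (1.960 + 1.282)² × (SD₁² + SD₂²/k) / δ², SD₁ = 2.38, SD₂ = 3.41 and k = n₂/n₁ = 0.8:
- n₁ = 10.507 × (5.664 + 11.628/0.8) = 212.2
- n₂ = 0.8 × 212.2 = 169.8

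The Welch t version gives exactly 214 and 172 (power 0.901). The figures thus reproduce with 214 attached to the conventional SD and 172 to the open access SD, the reverse of the labels. With the SDs as labelled, 158 and 197 would be needed, and 172 and 214 give about 92% power. This does not affect the present point.

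**2. Unadjusted comparison at 18 months.** In SD units, the standard error is √(1/172 + 1/214) = 0.1024. The difference detectable with 80% power is (1.960 + 0.842) × 0.1024 = 0.287 SD. Power for an illustrative 0.25 SD difference is Φ(0.25/0.1024 − 1.960) = 68.5%.

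**3. Adding the baseline score.** For a continuous score with baseline to 18-month correlation r, the variance of the adjusted arm difference is 1 − r² times the unadjusted one. A comparison of change scores has factor 2(1 − r), assuming equal SDs at both times. The article gives no r, so the values below are assumptions.

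| Assumed r | Factor 1 − r² | Variance cut | N giving the precision of 386 unadjusted | Detectable at 80% power | Power at 0.25 SD | Change-score factor |
|---|---|---|---|---|---|---|
| 0 (unadjusted) | 1.00 | none | 386 | 0.287 SD | 68.5% | 2.00 |
| 0.3 | 0.91 | 9% | 351 | 0.274 SD | 72.5% | 1.40 |
| 0.5 | 0.75 | 25% | 290 | 0.248 SD | 80.5% | 1.00 |
| 0.7 | 0.51 | 49% | 197 | 0.205 SD | 92.8% | 0.60 |
| 0.8 | 0.36 | 64% | 139 | 0.172 SD | 98.3% | 0.40 |

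The gain is modest at r = 0.3 and substantial from about 0.5. Baseline adjustment is never less precise than a change score. A change score is worse than ignoring the baseline when r is below 0.5.

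**4. Which outcomes this covers.** The formula suits the multi-item scales: WHO-5, GSE and the HLQ subscales. General health is one five-category item, patient activation is two ad hoc items, and seizures, side effects and the experience measures are also ad hoc items. For these the table is no guide to size, although adjusting for the baseline response is still sensible.

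**The case against.** The strongest objection is that the article does not say the baseline score goes unused. Regression is one of the permitted analyses and could carry it. The demographic covariate list is tied to the per-protocol analysis and does not define the secondary regressions. A t-test on change scores is not excluded either. A condensed article may also leave the covariates of secondary models to a fuller document. All of this stands. A reader might infer that the plan compares 18-month scores by t-test and ignores baseline, but the text does not support that reading. What remains is that the article does commit to a menu of tests, a normality-driven switch and one covariate list, and nothing in these states a use of the baseline score beyond description.

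The size of the gain is also open. A reader might call it large, but the documents give no correlation, and at r = 0.3 the variance falls by only 9%.

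Two further inferences fail. An unadjusted comparison of randomised arms is not biased, and its standard error already allows for chance imbalance. Patients without an 18-month response are a separate matter that baseline adjustment does not cure, since that model also needs the 18-month score.

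Finally, hypotheses 2 and 3 do not rest on these scores alone. Mortality comes from a register, and the article says the patient perspective is explored mainly by qualitative methods.

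**Conclusion.** The point holds as one of efficiency and clarity. The article leaves the analysis of continuous secondary outcomes to a choice among three methods, states no use of the baseline score in any of them, and names covariates only for the per-protocol analysis. A better method is available from data already scheduled.

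Its value for WHO-5, GSE and the HLQ subscales is a variance reduction of 9%, 25% or 49% at assumed correlations of 0.3, 0.5 or 0.7. The detectable difference would fall from 0.287 SD to between 0.274 and 0.205 SD, if all 386 patients contribute both scores. Non-response would worsen both the unadjusted and the adjusted figures. The primary outcome, a register count of contacts, is unaffected, and no bias in the randomised comparison is shown.

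**What to change.** In the Analyses section, replace the choice between t-test, regression and rank test for secondary scores with one stated intention-to-treat analysis:
- **WHO-5, GSE and each HLQ subscale:** a linear model (ANCOVA) of the 18-month score on randomised arm, with that scale's own baseline score as covariate, reporting the adjusted mean difference with its 95% confidence interval.
- **Single-item or categorical outcomes:** logistic or ordinal regression on arm with the baseline response as covariate.
- **Missing baseline score:** a simple rule that keeps such patients in the model, for example imputing the baseline value from the two arms combined.

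The normality-driven switch is then unnecessary for these outcomes. With 172 and 214 patients, the comparison of means does not depend on normally distributed scores.

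The cost is a change of wording made before the 18-month data are examined. No extra data or patients are needed, and the sample size stays as it is.

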**Fig. 2 Fig2:**
[figure not shown]
The open access telePRO website “My Epilepsy”. Note: Labels were translated from Danish

The website consists of four core elements:Answer questionnaire: Here, patients can answer the epilepsy questionnaire when they need to get in contact with the clinic. The questionnaire is the same as in standard telePRO. When the patient has completed the questionnaire, the response is automatically sent as a red request to the PRO alert list at the epilepsy clinic. The clinician assesses the response and contacts the patient as soon as possible. The clinic has reserved appointments in their booking system to ensure that patients get a quick appointment. As a “safety net”, patients have to answer the questionnaire before twice the fixed interval has elapsed. For example, if the patient is referred with a 12-month interval, the patient has to respond within two years. If not, the patient is automatically sent a questionnaire, given a red status, and is contacted by a clinician.Previous answers: In this element, all of the patient’s previous questionnaire responses are available. Patients have access to a PRO overview interface and specific and detailed questionnaire responses in the same manner as the clinicians. The overview interface is shown in Fig. 3. It is customised to monitor selected PRO data and to illustrate changes in health status over time. Colour codes indicate the severity of the symptoms reported by the patient. A red or orange bar indicates a self-reported problem, a yellow bar some problem, and green bar indicates no problems.

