### Randomisation

Pre-randomisation designs prevent change in behaviour in the control group because of disappointment about the allocation [19]. Eligible standard telePRO participants will be pre-randomised to standard telePRO follow-up (no change) or open access telePRO follow-up. Control as well as intervention participants receive the baseline questionnaire together with the fixed PRO questionnaire. The clinicians respond to the fixed PROs as usual and will not have access to the baseline questionnaire. Control participants will continue with fixed interval questionnaires and no change will be undertaken. Intervention participants will receive detailed information about the open access approach two weeks after a clinician’s response to the fixed PRO questionnaire. The study coordinator will forward written information to the included intervention participants. Individuals who not agree to participate will continue with standard telePRO follow-up. Due to the nature of the intervention neither patients nor clinicians can be blinded to allocation. The randomisation is performed with an algorithm developed as part of the WestChronic software [12]. The allocation ratio open access/standard is 0.55/0.45. This ratio was selected to account for an expected number of patients in the open access arm who do not wish to participate.

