### Ethics

The risks to participants are considered to be minimal as all eligible participants are referred to standard telePRO follow-up by clinicians at the epilepsy clinic. As a “safety net” to ensure that no patients are lost in the open access arm, the patients have to answer the epilepsy questionnaire before twice the fixed interval has elapsed. If lack of response the patient is reallocated into standard telePRO with a red status and a clinician will contact the patient. Furthermore, all patients are informed to call the clinic in pressing need of attention.

The Danish Data Protection Agency has accepted the study. In addition, the Danish research ethics committee in Central Denmark Region was contacted and has stated that approval from the committee is not necessary for this present study. Therefore, written informed consent was not obtained from the participants. Prior to study participation patients in the intervention group receive written information about the study. Study participation is entirely voluntary and participants are informed they can withdraw from the study at any time without affecting future care. In the qualitative complementary PhD study, the participants gave written informed consent prior to enrolment, and the study was approved by the Danish Data Protection Agency.

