## Discussion

During the last decade, the use of PRO in clinical practice has become increasingly common, and to our knowledge, AmbuFlex is the first generic PRO system that uses PRO as the basis for outpatient follow-up [13]. The focus of this trial will be to evaluate the effect of a patient-initiated open access telePRO intervention compared to standard telePRO with respect to resource utilisation, quality of care, and the patient perspective. Ideally, we would have preferred to compare the two arms (standard and open access) with conventional follow-up with pre-booked outpatient visits to the clinic. However, this was not possible because the epilepsy clinics in Central Denmark Region have used standard telePRO follow-up since 2012. Thus, we will compare two rather similar outpatient follow-up activities, which will probably result in only small differences in effect between the groups. Evaluation of the effect must be done using reliable, valid, and clinically meaningful measures. This study includes outcome measures based on recommendations from clinical experts, researchers, and the literature [33].

Loss to follow-up is one of the main concerns in randomised controlled studies [34]. Loss to follow-up in this study is related to the open access group of patients since study participation in the open access arm is entirely voluntary, and participants can choose to continue with standard telePRO follow-up. Loss of statistical efficiency can be overcome by increased the number of participants in the study [19]. We have taken this into consideration and will include 10% more patients in the open access telePRO arm. In addition, we will recruit a larger number of participants than the minimum sample size calculation indicated.

Only web-responders will be included in the open access arm, and the results may therefore be generalizable only to this subgroup of epilepsy patients. These patients may differ with respect to education, age, and use of new technologies compared to the entire group of epilepsy patients. In another study in progress, the aim is to examine determinants for referral to telePRO follow-up. Data from this study can be used to compare the study population with the entire group of patients with epilepsy.

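### A per-protocol contrast adjusted for five demographics does not guard against selective refusal in the open access arm; a complier estimate from all randomised patients would serve better

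*Protocol article*

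**What the plan says.** The Abstract (Methods) names intention to treat and per-protocol together as the bases for analysis. The Analyses section puts intention to treat first, with every randomised patient kept in the allocated arm. It mentions the per-protocol analysis only to fix its adjustment set: "Demographics covariates (sex, age, education, marital status, and epilepsy diagnosis duration) will be included in the per- protocol analysis".

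The Randomisation section describes pre-randomisation. For controls, "Control participants will continue with fixed interval questionnaires and no change will be undertaken". Only the open access arm receives an offer, and for those who turn it down, "Individuals who not agree to participate will continue with standard telePRO follow-up". Allocation is 0.55/0.45 in favour of open access because some of that arm is expected to decline. No expected rate is given.

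The Discussion treats this as attrition: "Loss to follow-up in this study is related to the open access group of patients". Its remedy is more participants overall, and it says the trial "will include 10% more patients in the open access telePRO arm".

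The primary outcome, number of contacts, comes from a hospital register (Primary outcome section and Table 1).

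On patients who let twice their interval pass without answering, the Ethics section says "If lack of response the patient is reallocated into standard telePRO with a red status". The description of the website's questionnaire element says "the patient is automatically sent a questionnaire, given a red status, and is contacted by a clinician" and does not mention reallocation.

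**The concern.** Decliners receive the control condition and remain visible in the register. For the primary outcome they are non-compliers, not missing data.

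Non-compliance can occur in one arm only. A per-protocol set formed in the usual way would remove decliners from open access. Their counterparts in the control arm, who would have declined if asked, cannot be identified and would stay in. The contrast would then be acceptors against a mixture of would-be acceptors and would-be decliners, which is no longer a randomised comparison.

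The five covariates are demographic apart from duration of diagnosis. They do not include previous contacts, seizures, side effects or the assigned questionnaire interval (3, 6 or 12 months), all of which plausibly bear on how often a patient contacts the clinic. The Discussion itself reports that some patients find security in the fixed questionnaire, so accepting open access is plausibly related to contact behaviour.

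Two things are at stake. A per-protocol estimate of the saving could be wrong in either direction. And if refusal is thought of as lost numbers, its effect on the intention-to-treat contrast, which is dilution, may not be allowed for.

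**Working it through.** **Inputs from the Sample size and Randomisation sections:** SD 2.38 (conventional follow-up) and 3.41 (open access), difference 1 contact, power 90%, alpha 0.05 (taken as two-sided), sample-size ratio 0.8, 172/214 required, about 500 recruited. At 0.55/0.45 that is 275 open access and 225 standard.

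**Assumed, because the article gives neither:** the refusal share r (10% to 40%), and the gap D, the mean contacts under standard care of decliners minus those of acceptors (+1 or -1).

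**The plan's own figure.** n_standard = (SD_standard² + SD_open²/1.25) × (1.960 + 1.282)².
- SDs as labelled: (5.664 + 9.302) × 10.51 gives 158, with 198 in open access.
- SDs crossed between arms: (11.628 + 4.532) × 10.51 gives 170/213. The Welch t version needs 214 in open access and 0.8 × 214 = 171.2, rounded up to 172.

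So 172/214 reproduces only with the SDs crossed. This is conservative (172/214 gives 92% power with the SDs as labelled) and does not affect the present point.

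**What each estimator targets.** Let the effect in acceptors be -1 contact, and let the offer alone change nothing in decliners.
- Intention to treat: -(1 - r)
- Acceptors against all controls, unadjusted: -1 - rD
- Complier estimate: intention-to-treat difference / (1 - r)

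| r | ITT | Per-protocol, D = +1 | Per-protocol, D = -1 | Complier |
|---|---|---|---|---|
| 0.1 | -0.90 | -1.10 | -0.90 | -1.00 |
| 0.2 | -0.80 | -1.20 | -0.80 | -1.00 |
| 0.3 | -0.70 | -1.30 | -0.70 | -1.00 |
| 0.4 | -0.60 | -1.40 | -0.60 | -1.00 |

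The per-protocol bias is -rD. At r = 0.3 it is 0.30 contacts, towards a saving if decliners make more contacts and away from one if they make fewer. The match with ITT at D = -1 arises only because the gap equals the effect in size.

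**False-positive rate of the per-protocol test** (no true effect, r = 0.3, gap of one contact, covariates removing none of it): SE = √(2.38²/225 + 3.41²/192.5) = 0.293. The bias is 0.30/0.293 = 1.03 standard errors, and the two-sided error rate is about 18%. The sign of D decides whether the spurious result looks like a saving or an increase.

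**Precision.** In simulation with 275/225, r = 0.3 and D = +1, the standard errors were about 0.26 (ITT), 0.30 (per-protocol) and 0.36 (complier).

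**Power of intention to treat if the one-contact difference applies to acceptors.** SE = √(2.38²/225 + 3.41²/275) = 0.260; power = Φ((1 - r)/0.260 - 1.96).

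| r | 0 | 0.1 | 0.2 | 0.3 | 0.4 |
|---|---|---|---|---|---|
| Power | 97% | 93% | 87% | 77% | 64% |

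Power of 90% requires 1 - r ≥ 0.260 × 3.24 = 0.84, so r up to about 16% (13% with the SDs crossed). Required numbers grow as 1/(1 - r)². At r = 0.3 that is 158/0.49, or 321 in the standard arm with the SDs as labelled, against 225 planned.

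**The case against.** The strongest reply is that the plan already protects its main conclusion. Intention to treat in all randomised patients is stated, and the Discussion answers refusal with a larger sample and unequal allocation. A reader might infer that the per-protocol analysis is how refusal is handled, or that it ranks as a second main analysis. The article supports neither: one abstract sentence lists the two bases together, and the Analyses section leads with intention to treat. This part of the reply stands.

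A reader might also take it as fact that decliners and lapsed patients are dropped. No section defines the per-protocol set, and an article may leave that to a fuller document. Excluding decliners is the conventional reading, so the point is conditional on it.

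Nor do the documents show that the per-protocol result would exaggerate the saving. The sign of the gap is unknown, and the covariates may remove part of it.

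It is tempting to read 18% expected refusal out of the allocation, since 0.55 × (1 - 0.18) is about 0.45. The article does not say that equal arms after refusal were the aim, and its own requirement of 172/214 is unequal.

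The expected one-contact difference is described as between the groups, which can be read as the intention-to-treat contrast itself. On that reading no further dilution applies, so the power figures are conditional too.

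The loss-to-follow-up label could be apt for questionnaire outcomes if decliners do not return them. It is not apt for the register-based primary outcome.

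Finally, the complier estimate has its own assumption and is no more powerful than intention to treat. That is true, but it uses every randomised patient, and its assumption can be stated openly. The per-protocol contrast needs decliners and acceptors to have equal expected contacts given five covariates, which is harder to defend here.

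**Conclusion.** The point holds as a weakness in a stated supplementary analysis and in how refusal is described. It is not a flaw in the primary analysis. If the per-protocol set excludes decliners, its estimate for number of contacts carries a bias equal to the refusal share times the contact gap, less what the five covariates remove. Under the assumed 10% to 40% refusal and a gap of one contact, that is 0.1 to 0.4 contacts before adjustment, in either direction, against an expected effect of one. The design supports a better estimate: the offer is randomised, no control access to open access is described, and register outcomes cover decliners.

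If the one-contact difference is meant for patients who use open access, 500 patients give 90% intention-to-treat power only up to about 16% refusal, assuming no other attrition.

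Two minor wording points go with this. The Discussion's 10% is correct only as percentage points (55% against 45%); as a ratio, 275/225 is 22% more. The Ethics section and the website description differ on whether lapsed patients are reallocated. The practical reach is limited: with a 12-month interval the limit is 24 months, beyond the 18-month follow-up, so only patients on shorter intervals can lapse within the outcome window.

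**What to change.** - Keep intention to treat in all randomised patients as the primary analysis.
- For number of contacts, report a complier average causal effect instead of the per-protocol estimate, or ahead of it if per-protocol is retained as exploratory. Use randomised arm as the instrument for accepting open access (two-stage least squares, or the intention-to-treat difference divided by the acceptance share). Include all randomised patients and keep lapsed patients as acceptors. State the assumption that the offer alone does not change decliners' contacts. The ratio is defined on means, so report the mean difference even if skewness leads to a rank test.
- Call refusal non-compliance where the primary outcome is concerned.
- Say whether the one-contact difference refers to the randomised groups or to users of open access. If the latter, give the intention-to-treat power across 10% to 40% refusal.
- Express the allocation difference as 10 percentage points, and reconcile the Ethics section with the website description on lapsed patients.

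The cost is analysis wording plus a record of who accepted. The two follow-up pathways presumably require that record, although the article does not describe how it is kept. The downside is a wider interval than per-protocol (standard error about 0.36 against 0.30 at 30% refusal) and no gain in power over intention to treat.
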